**Figure 2: The Stepped-Wedge Design**

[figure not shown]

A parallel design for this study was deemed unsuitable for both scientific and logistical reasons. Scientifically, because of the possibility, even likelihood, that in a parallel design the different groups of physiotherapists would be found to be unbalanced on some covariates, whereas the crossover designs have balance, reducing the influence of confounding variables because each physiotherapist subject serves as his or her own control (Brown et al., 2008). This is particularly important for this study as it could be argued that individual therapist attributes could have the greatest impact on patient outcomes. Logistically, the statistical efficiency of crossover designs requires fewer subjects than parallel designs; in a study requiring the use of available qualified clinical staff, and highly qualified clinical mentors, this would appear to be a valid consideration for design selection (Jones and Kenward, 2003). The stepped-wedge design was selected for four main reasons:

1. There is not a belief of equipoise – that is, it is rational to believe that the intervention is likely to result in good rather than harm for both the participating physiotherapists, who will receive Master’s level mentoring, and the clusters of patients “exposed” to the physiotherapists who have received training, making a parallel CRCT ethically less acceptable in that it would withhold the intervention from a larger proportion of physiotherapists and patients (Mdege et al, 2011; Brown & Lilford, 2006).
2. While a standard crossover CRCT would also satisfy this ethical concern, it would require the delivery of the intervention at the same time; this is logistically and practically difficult as the intervention (clinical reasoning facilitation via a mentoring programme) requires both specialist input (experienced MACP qualified mentors) and significant time input (150 hours of clinical mentoring), making the stepped-wedge design preferable as the intervention can be delivered in stages (Mdege et al, 2011; Hussey and Hughes, 2007; Brown and Lilford, 2006).
3. The stepped wedge design has been used for scientific reasons such as to allow detection of underlying trends or control for time effects (Brown and Lilford, 2006, Mdege et al., 2011); this is of interest in the current study, as the multiple time points of data collection will allow for investigation of time effects to answer relevant questions– for example, does the effect dissipate over time, or does the intervention require time to consolidate and therefore have impact on patient outcomes.
4. Another advantage of the stepped wedge design over a parallel CRCT is that it requires fewer clusters (Hussey & Hughes, 2007), and it maximises power as the intervention effect is estimated on both between-cluster and within-cluster comparisons (Mdege et al, 2011; Pearson et al, 2010).

## Methods - Participants

There are some key questions to be clear in answering in the design of CRCTs: what is the unit of randomization, how and to whom is the intervention delivered and how and on whom is the outcome measured (Hussey and Hughes, 2007)? In this study, the physiotherapy sites (departments) are the unit of randomisation, the intervention is delivered to participating physiotherapists in these clusters, and the outcome is measured on clusters of consenting patients who are treated by these physiotherapists.

### Eligibility criteria for participant clusters

As expertise is generally accepted to be context dependent (Alderson, 2010, Benner et al., 1996, Edwards and Jones, 2007, Eraut, 2006b, Jensen et al., 2007b, Resnik, 2007), all qualified physiotherapy staff from the Cardiff and Vale University Health Board whose majority of time (i.e. greater than 50%) is practised inside the musculoskeletal outpatient context will be eligible to participate in this study. There are two main exclusion criteria, namely members of staff who have already undertaken postgraduate placements as part of Master's education and so would have received similar clinical reasoning facilitation, and rotational staff due to the fact that they will not be present in the department for long enough for both interventions and long term follow up. Currently, the maximum potential number of participating therapists would be 18. It is envisaged that 12 physiotherapists would realistically be recruited and organized into 3 clusters of physiotherapy staff (clustering by site).

### Eligibility criteria for patient clusters

Consecutive consenting patients attending the outpatient musculoskeletal physiotherapy service at the Cardiff and Vale University Health Board for treatment by the participating physiotherapists during data collection periods towards the end of each step will be eligible to participate. The main exclusion criteria would be patients under 18 years of age, and patients who are not English-literate due to the validity of the Outcome Measures being established only for the English language and for adults.

### Settings and locations where the data will be collected

Patient outcome data will be collected at the first and last appointment of physiotherapy treatment at the six sites of outpatient musculoskeletal physiotherapy service delivery for the Cardiff and Vale University Health Board: The Barry Hospital, Cardiff Royal Infirmary, University Hospital Llandough, St. David's Hospital, University Hospital of Wales and Whitchurch Hospital. The 6 sites are organized into pairs for training purposes, and so to further reduce the risk of any potential contamination across sites, these pairs will form the 3 clusters which will be the unit of randomization as illustrated in figure 3. Long-term patient outcome data (12 months post-discharge) will be collected by participating physiotherapists by telephone contact.

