### Procedures

It is the *differences* in patient outcomes data that is being measured. Outcomes data will be collected from a cluster of patients being treated by each participating therapist at each stage of the stepped wedge design, giving 4 clusters of patient data per physiotherapist cluster for within group and between group comparison.

For each patient, outcome data will be collected at first and last appointment and at 12 months post discharge. The long term follow up is important in that – as Resnik (Resnik, 2007) points out - it is possible that aspects of physiotherapy intervention (for example, patient education) have health effects which are lifelong and therefore cannot be measured purely with discharge measurements of the patient's status. All patients treated sequentially by the therapist will complete the outcomes until a full data set is obtained.

Patient data loss from failure to complete treatment / DNA will be minimized by telephone contact, having consented patients to being contacted by the researchers by telephone as part of the study follow up. Patients refusing to complete data or withdrawing consent will be reported as will the reasons for failure to complete treatment and / or outcomes.

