### **Blinding (Masking)**

As with all other evaluations, masking patients, caregivers and observers, as well as those undertaking the statistical analysis is important in minimising information bias (Schulz et al., 2002, Schulz and Grimes, 2002). Due to the fact that in stepped wedge trials the timing of intervention rollout is the unit of randomization, the participating physiotherapists and intervention implementers (clinical mentors) are aware of which cluster is receiving the intervention (Brown et al., 2008, Mdege et al., 2011). However, it is possible to blind the outcome assessors, in this case the lead researcher (who will be unaware of the sequence allocation when analysing outcome data) and the independent observer of physiotherapist performance. This blinding of outcome assessors and use of sequence generation and allocation concealment is essential to enhance internal validity (Brown et al., 2008). Patients submitting their outcomes will also be unaware of whether or not their allocated physiotherapist has received his/her intervention.

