## **Validity approaches in quantitative methods: Identification of threats to validity and responses**

Creswell (2009) identifies common threats to both internal and external validity. Of particular relevance to this study, internal threats could be due to history, selection, compensatory processes, testing or instrumentation. History threats can be due to external events that can occur during the time that elapses in an experiment, which have an impact on the outcome besides the experimental treatment. To counter this, the research design uses participants from a single profession (physiotherapy), working in a similar environment (musculo-skeletal outpatient departments) in the same NHS health board (Cardiff and Vale); this means that professionally and organizationally the participants should experience the same external events. Selection threats can be due to participants being selected who have certain attributes that predispose them to have better outcomes (e.g., he or she is already more advanced in clinical reasoning, or is brighter or more likely to respond to this form of educational intervention), thus increasing the risk of bias as highlighted by the Cochrane risk of bias tool (Armijo-Olivo et al., 2010, Lundh and Gotzsche, 2008). To counter this, the study has utilised a stepped wedge design (using a one way crossover), so that each participant acts as his / her own control. This does raise the interesting question of different participants' learning styles having a hidden but profound effect on learning effectiveness, and this will be explored using a learning styles questionnaire (Honey and Mumford, 2000a, Honey and Mumford, 2000b). Compensatory threats occur when benefits provided in the experimental group leave participants in the control group resentful, demoralized or feeling devalued, skewing results. Again, the stepped wedge design of this trial counters this threat, with each participant acting as their own control, meaning benefits are provided to both groups, and the fact that during the control phase of this process usual training is being received. Testing threats occur when participants become familiar with the outcome measure being used and remember their responses for later testing. This is countered by the primary outcome measures being *patient* completed outcome measures, and the long-term follow up meaning that recall of previous responses is highly improbable. Instrument threats occur with changes in outcome measures between a pre-test and post-test; in this case, a broad range of outcomes are used to make any desire for changes in outcome measures unnecessary.

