|-----------------------------|----------------|
|                             |                |
|                             |                |
|                             |                |
|                             |                |
|                             |                |
|                             |                |

**Functional Scale:** Your physiotherapist will complete this with you to identify up to three important activities that you are unable to do or are having difficulty with as a result of your problem. Your physiotherapist will ask you some questions to help you rate how difficult those activities are.

| Activity | Initial Score: | Current Score: |
|----------|----------------|----------------|
| 1.       |                |                |
| 2.       |                |                |
| 3.       |                |                |

Please read and answer questions carefully. Do not take too long to answer the questions; however it is important that you answer every question. There is **always** a response for your particular situation.

☐ Neck
 ☐ Shoulder
 ☐ Arm
 ☐ Upper Back  
☐ Lower Back
 ☐ Leg
 ☐ Other (state)

☐ 0 days (1)      ☐ 1-2 days (2)      ☐ 3-7 days (3)      ☐ 8-14 days (4)

☐ 15-30 days (5)      ☐ 1 month (6)      ☐ 2 months (7)      ☐ 3-6 months (8)

☐ 6-12 months (9)      ☐ over 1 year (10)

☐ 0-1 weeks (1)      ☐ 1-2 weeks (2)      ☐ 3-4 weeks (3)      ☐ 4-5 weeks (4)

☐ 6-8 weeks (5)      ☐ 9-11 weeks (6)      ☐ 3-6 months (7)      ☐ 6-9 months (8)

☐ 9-12 months (9)      ☐ over 1 year (10)

0 1 2 3 4 5 6 7 8 9 10  
Not at all Extremely

| 0       | 1 | 2 | 3 | 4 | 5 | 6 | 7 | 8 | 9 | 10                         |
|---------|---|---|---|---|---|---|---|---|---|----------------------------|
| No pain |   |   |   |   |   |   |   |   |   | Pain as bad as it could be |

| 0                          | 1 | 2 | 3 | 4 | 5 | 6 | 7 | 8 | 9 | 10 |
|----------------------------|---|---|---|---|---|---|---|---|---|----|
| No pain                    |   |   |   |   |   |   |   |   |   |    |
| Pain as bad as it could be |   |   |   |   |   |   |   |   |   |    |

0 1 2 3 4 5 6 7 8 9 10  
Never Always

0 1 2 3 4 5 6 7 8 9 10

Can't decrease it at all Can decrease it completely

0 1 2 3 4 5 6 7 8 9 10

Absolutely calm and relaxed As tense and anxious as I've ever felt

0 1 2 3 4 5 6 7 8 9 10

Not at all Extremely

0 1 2 3 4 5 6 7 8 9 10  
No risk Very large risk

0 1 2 3 4 5 6 7 8 9 10

No chance Very large chance

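### The stated assessor blinding does not reach the PSFS: physiotherapists who know the allocation help patients rate the primary outcome and telephone for the 12-month data

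*Protocol*

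**What the plan says.** **How the PSFS is taken.** The Functional Scale in the baseline questionnaire tells the patient: "Your physiotherapist will complete this with you to identify up to three important activities that you are unable to do". On scoring it adds: "Your physiotherapist will ask you some questions to help you rate how difficult those activities are". The grid has a column for the initial score next to one for the current score. Procedures (under Secondary Outcome Measures) has outcome data taken at the first and last appointments and 12 months after discharge.

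**Who collects at 12 months.** Settings and locations says: "Long-term patient outcome data (12 months post-discharge) will be collected by participating physiotherapists by telephone contact". Procedures, on limiting data loss, speaks of "having consented patients to being contacted by the researchers by telephone as part of the study follow up".

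**Who is blinded.** Blinding (Masking) accepts that "the participating physiotherapists and intervention implementers (clinical mentors) are aware of which cluster is receiving the intervention". It then says that "it is possible to blind the outcome assessors, in this case the lead researcher", who does not know the sequence when analysing, together with the independent observer of physiotherapist performance. It treats this blinding as indispensable to internal validity. It also states that patients will not know whether their physiotherapist has had the intervention.

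**What the validity section relies on.** Validity approaches in quantitative methods answers the testing threat by pointing to the primary measures being patient "completed outcome measures, and the long-term follow up meaning that recall of previous responses is highly improbable". The same argument is repeated in the later section on validity, credibility and trustworthiness.

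**The concern.** The PSFS is a patient rating, but on the form shown it is obtained in conversation with the physiotherapist. That person is the one under evaluation, has been told that patient outcome is the variable of interest (Deviation from normal experience – Therapist perspective), and knows whether he or she has been mentored. The protocol also says, in its reasons for the design, that equipoise is absent because benefit is expected. These are the conditions in which prompting and politeness can move a rating.

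The blinding section gives the impression that outcome assessment is masked. For the PSFS it is not: analysing ratings blind cannot undo an influence present when they were given. A rating shift that follows the therapist's mentored status would enter the model through the same indicator as the intervention, and risk adjustment on patient characteristics would not remove it.

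**Working it through.** **1. Who touches the rating, and who is blinded**

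| Role | Takes or influences a PSFS rating? | Blinded, per the protocol? |
|---|---|---|
| Patient | Gives it | Yes, unaware of therapist's status |
| Treating physiotherapist | Helps the patient rate (baseline questionnaire) | No |
| Participating physiotherapist, 12-month call | Collects it by telephone | No |
| Lead researcher | No; analyses it | Yes, at analysis |
| Observer of therapist performance | No; scores the therapist | Yes |

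The only masked person in the chain that produces the rating is the patient.

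**2. What kind of shift would matter**

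Procedures says that differences in outcome are what is measured. Suppose a mentored therapist's way of eliciting ratings moves the first-visit score by *a* and the last-visit score by *c*, relative to the same therapist before mentoring. The change score moves by *b = c − a*.

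- If *a = c*, then *b* = 0 and there is no bias. Patients are recruited towards the end of each step, after mentoring, so the same therapist in the same status would normally take both scores. A constant habit of elicitation therefore cancels.
- If *a* = 0 and *c* > 0 (encouragement when progress is being judged), then *b = c*. In the protocol's model the indicator X goes from 0 to 1 at crossover, so *b* is added to the estimated intervention effect.

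**3. The protocol's own precision, reproduced**

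Inputs from the power calculation and Appendix E: I = 12, T = 4, N = 9, within-group SD 2, tau = 1, U = 24, W = 224, V = 56; so s² = 4/9 = 0.4444.

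Var = I·s²·(s² + T·tau²) / [(I·U − W)·s² + (U² + I·T·U − T·W − I·V)·tau²]

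- Numerator: 12 × 0.4444 × 4.4444 = 23.704
- Denominator: (288 − 224) × 0.4444 + (576 + 1152 − 896 − 672) × 1 = 28.444 + 160 = 188.444
- Var = 0.125786; SE = 0.35466; 1/SE = 2.8196; power = 0.805; 4 × 12 × 9 = 432 observations

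These match the protocol.

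**4. Illustration of size (b is assumed)**

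With a true effect of zero, D = b/0.35466 and P(reject) = 1 + Φ(−1.96 − D) − Φ(1.96 − D).

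| Assumed net shift b (points) | Share of the 1-point target | D | False-positive rate |
|---|---|---|---|
| 0 | 0% | 0 | 5.0% |
| 0.1 | 10% | 0.282 | 5.9% |
| 0.25 | 25% | 0.705 | 10.9% |
| 0.5 | 50% | 1.410 | 29.2% |

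**5. The 12-month call**

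Steps last 12 months, with data collected at the end of each. Three clusters crossing at steps 2, 3 and 4 give 1 + 2 + 3 = 6 control cluster-periods. Patients from each cluster's last control period (3 of the 6) fall due for their call at about the time their cluster is completing its first mentored step. If callers come from the treating cluster, the caller's status then no longer matches the patient's exposure. That tends to even out any caller effect between phases; it does not inflate the contrast. The problem at 12 months is that ratings are collected by unblinded participants, not that the bias has a known direction.

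**The case against.** The strongest counter-argument is that the score is the patient's and the protocol says patients are masked. This is right as far as it goes: the therapist helps and does not score, and patient unawareness removes the patient's own expectation of a better-trained therapist. It does not remove the influence of a therapist who does know. The cancellation in step 2 also stands and narrows the concern to a shift specific to the last visit.

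Several stronger readings are tempting but are not supported:

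- *That the protocol claims whoever collects the PSFS is blinded.* It does not. It is open about therapist awareness and applies the term outcome assessor loosely to the analyst.
- *That describing the measures as patient completed is a false claim of blinding.* The phrase answers a threat about remembered responses. It fits the assisted procedure poorly but is not a statement about masking.
- *That patients are told the researchers will telephone.* Procedures is protocol text about data loss, and the patient information sheet is not available here. What exists is an inconsistency between two sections over who makes contact.
- *That the last-visit procedure is known.* The form shown is headed as the baseline version, and Table 6 refers to separate discharge and 12-month questionnaires that are not visible. Therapist help at the last visit, with the initial score in view, is inferred from the current-score column. That satisfaction items are asked by telephone is likewise an inference.
- *That the 12-month caller is the patient's own therapist, or that this limb affects the primary result.* The protocol says neither.

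**Conclusion.** The concern holds in a limited form. On the text, the primary outcome is elicited with an unblinded physiotherapist who is under evaluation, 12-month data are collected by participating physiotherapists, and the assessor blinding the protocol relies on covers neither. Patient unawareness and the use of change scores reduce the exposure but do not close it.

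No size can be given from the document. The rates of about 6%, 11% and 29% rest on assumed net shifts of 0.1, 0.25 and 0.5 points, on the protocol's standard error of 0.355, and on a true effect of zero. At the low end the rate is close to nominal. A reader should not take the upper figures as an estimate of the trial's error rate, nor conclude that any difference in elicitation must bias the result; only a shift that differs between first and last visit does so. The case for change rests on a cheap protection for the primary outcome, since ratings already given cannot be repaired at analysis.

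**What to change.** 1. **First visit:** let the physiotherapist help the patient name the activities.
2. **Last visit:** the patient completes the PSFS ratings and the other scales alone, on a sheet that lists the named activities but not the initial score, and returns it sealed to reception.
3. **12 months:** use postal self-completion. Alternatively, use callers from existing staff at another site pair who did not treat the patient and are not shown the patient's study period. The questionnaire header carries a therapist ID and a cohort number, so the call sheet should show only the patient identifier and the named activities.
4. **Text:** name the same party for telephone contact in Settings and locations and in Procedures. Reword Blinding (Masking) so that it limits the claim to blinded analysis and blinded scoring of therapist performance, and does not imply blinded assessment of the PSFS. In both validity sections, make the description of the primary measure as patient completed agree with the procedure adopted.

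The cost is a form change, a call-allocation rule and possibly a slightly lower 12-month response if post is used. The planned 432 observations and the power of 0.805 are unaffected.

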**Figure 3: The stepped-wedge design for the quantitative component of the study**

[figure not shown]

## Methods - Interventions

### Intervention

The first step (time point) corresponds to a baseline measurement where none of the clusters receive the intervention, which is usual practice for this design (Hussey and Hughes, 2007). At each subsequent step a cluster of participating physiotherapists (a department of the MSK outpatient physiotherapy service) will cross over from control to receive the intervention - a 150 hour clinical mentorship programme, aimed at facilitating clinical reasoning. This will be delivered to participating physiotherapists by mentors who are MACP members, having qualified at MSc / PgD level from a higher education establishment, and who have experience in delivering this form of mentorship at post-graduate level. The intervention will be delivered at the start of the time period, to allow for consolidation and application of the programme, before data collection occurs at the end of the time period. This intervention is selected on the basis that the use of mentorship in the context of clinical placement is established practice in Master's programmes seeking to develop expert practice and has strong support from qualitative literature as outlined earlier. The intervention will take place in the usual clinical context of the participating physiotherapists (as is current practice), consisting of the mentors observing the participating physiotherapists assessing and treating new and follow-up patients, discussing and facilitating clinical reasoning processes immediately after the patients have left. While this programme needs to be fluid enough to address identified learning needs and errors in clinical reasoning, a framework on which to hang discussion, feedback and reflection sessions will help to standardize the intervention to a point; the dialectical clinical reasoning model of Jones and Edwards, 2007 (see figure 4 below) will be implemented to this end. This model has been selected due to its flexibility for management and assessment paradigms, its adaptability to patient situations and presentations, and its underpinning research (Edwards et al., 2004, Edwards et al., 2006, Edwards and Jones, 2007). Failure of participants to receive the intervention will be reported, as well as the reasons for such failure.

